**Figure 2 figure2:**
[figure not shown]
Just-in-time intervention algorithm. EOD: end of day. NA: negative affect; PC: perseverative cognition; RRP: reactivity, recovery, and pileup; SS: subjective stress.

**Figure 3 figure3:**
[figure not shown]
End-of-day (EOD) intervention algorithm. EMA: ecological momentary assessment; NA: negative affect; PC: perseverative cognition; RRP: reactivity, recovery, pileup; SS: subjective stress.

During the final week of the 3-week study period, the delivery of the JIT intervention content will cease (access to the web-based stress management education module will continue), and participants in both conditions will continue to engage in self-monitoring only. This final week of self-monitoring will provide information about the short-term impact of the JIT intervention and the immediate effects of tapering JIT intervention content. It will also evaluate whether any effects persist in whole or in part once the JIT intervention ceases. At the end of the 3-week study period, participants will attend a final session to return their devices and debrief about the study. A research assistant will assess participant compliance with the study procedures, and participants will receive their earned compensation of up to US $300 for phase 2.

#### Follow-Up

One month after the completion of phase 2, participants will be invited via email to complete a web-based follow-up self-report survey to assess changes in stress, sleep, and physical activity with measures capturing key study constructs. Participants will have 1 week to complete this survey to receive US $15 compensation.

### Measures

#### Demographics

At baseline, participants will provide information on the following demographic characteristics: sex, age, race, ethnicity, education level, current work status, household income, subjective social status, marital status, number of adults and children in the home, and height and weight (ie, BMI). We will also inquire about active gymnasium memberships and the use of wearables and smartphone apps for sleep and physical activity.

#### Baseline and Follow-Up Measures

The measures selected for this study are intended to capture a broad range of constructs that may impact stress and stress responses in everyday life, including personality, mood and affect, tendencies for ruminative and perseverative thinking styles, social support, and current stress. These person-level factors will help characterize our sample and may serve as potential explanatory variables for treatment response heterogeneity. We are also capturing information on current health status and preintervention and follow-up measures of self-reported sleep behaviors and sleep disturbance, physical activity behaviors, and physical activity intention or automaticity. The measures being assessed in this study and their assessment schedule are summarized in Table 1.

**Table 1 table1:** Study measures.

Construct and scale name		Baseline	Follow-up
Health status (SF-36^a^ [19])		✓	✓
Social support (Social Support Questionnaire [20])		✓	✓
**Personality**			
	The Satisfaction with Life Scale [21]	✓	
	Life Orientation Test-revised [22]	✓	
	Big Five Inventory [23]	✓	
	Rosenberg Self-Esteem Scale [24]	✓	
**Mood and affect**			
	Positive and Negative Affect Scale [25]	✓	✓
	Toronto Alexithymia Scale [26]	✓	
**Perseverative cognition**			
	Recent Perseverative Cognitions	✓	✓
	Perseverative Thinking Questionnaire [27]	✓	
	Rumination-Reflection Questionnaire (Rumination subscale) [28]	✓	
**Stress**			
	Recent stress	✓	✓
	Current stress	✓	✓
	Stress mindset [29]	✓	✓
	Impact of Events Scale [30]	✓	✓
	Perceived Stress Scale [31]	✓	✓
**Sleep**			
	Insomnia Severity Index [32]	✓	✓
	Pittsburgh Sleep Quality Index [33]	✓	✓
**Physical activity**			
	International Physical Activity Questionnaire [34]	✓	✓
	Physical activity intentions	✓	✓
	Generic Multifaceted Automaticity Scale [35]	✓	✓
Acceptability (General acceptability)			✓

^a^SF-36: 36-Item Short Form Survey Instrument.

#### Smartphone Surveys

##### Overview

The smartphone surveys in this study capture momentary and global ratings of stressful events, subjective stress, positive and negative affect, perseverative cognitions, and health behaviors as participants go about their daily lives. There are 2 types of smartphone surveys in this study, including those that are self-launched by the participant by button press within the smartphone app (ie, morning and evening surveys) and those that are automatically delivered to the participant at semirandom intervals throughout the day (ie, beeped surveys). The self-launched surveys serve as broader retrospective assessments of these outcomes across the day. In contrast, the beeped surveys are meant to capture more proximal assessments of these outcomes in the contexts in which they occur (at the moment). The information collected in the smartphone surveys will be used to derive our indicators of stress in real time and inform the delivery of JIT intervention content (Figures 2 and 3).

##### Morning Survey

Participants will be asked to launch and complete the morning survey each day within 30 minutes of waking. This survey will assess the duration and quality of the previous night’s sleep, current stress, affect, perseverative cognitions, plans for physical activity, and expectations for the day ahead.

##### Beeped Surveys

The beeped surveys will be automatically delivered to participants at 6 random times each day between 8 AM and 9 PM during the study period and are scheduled at semirandom intervals (1 to 4 hours apart; typically 2.5 hours apart) to capture most waking hours. These brief surveys assess the participant’s current location, activities, social interactions, recent stressors, affect, perseverative cognitions, and physical activity (duration and intensity). Participants can delay (up to 15 minutes) or dismiss any survey if they cannot complete it at the indicated time.

##### Evening Survey

Participants will be asked to complete the evening survey each night before going to bed and instructed to think about their entire day (ie, from waking up) when completing the survey. This survey assesses stressful experiences and reactions to them; overall day-level affect and perseverative cognitions; physical activity (duration and intensity); consumption of caffeine, nicotine, and alcohol; use of backlit devices before going to bed; and daytime nap duration.

#### Objective Sleep

Two research staff (who have been satisfactorily trained on scoring sleep data by a sleep expert on our team) will independently score downloaded data from the sleep watch. Sleep intervals and relevant sleep outcomes will be derived using a previously validated algorithm [36]. Outcomes will include total sleep time, wake after sleep onset, sleep efficiency, and nap count or frequency and duration. Total sleep time will be calculated by the number of minutes between sleep onset and awakening. Wake after sleep onset is the total time spent being awake between sleep onset and awakening. Finally, sleep efficiency will be calculated as the proportion of actual sleep from sleep onset to awakening relative to the total sleep duration interval (%). Naps will be delineated as other sleep periods >30 minutes in length that occur outside of the main nighttime sleep period.

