#### Proposed Analyses and Analytical Approach

All collected data will be subjected to a rigorous data-cleaning procedure to identify invalid data points (eg, out-of-range, implausible, and outlier variables will be scrutinized). General descriptive statistics (ie, mean, median, percentages, and SD) will be used to characterize the study sample. To evaluate the effect of the smartphone-delivered JIT intervention on RRP (specific aim 1), we will use mixed-effects models to evaluate any significant differences in RRP scores between the 2 study groups (ie, intervention group vs control group). In addition to the main effect differences between the 2 groups, we are interested in the potential cumulative effect of receiving multiple interventions across the 2-week study duration (testing a “dose” effect of the microinterventions) or whether potential benefits do not occur immediately but rather develop during the intervention period (eg, if it takes some time for the JIT intervention to lower stress responses). To evaluate this latter effect, we will test the group-by-time interaction effect in a multilevel (eg, momentary RRP nested within days, days nested within person, and person nested in group) mixed effect model. Analyses will be conducted using the SAS statistical program (version 9.4; SAS Institute Inc).

For our second aim, evaluating whether the intervention is associated with improved health behavior levels (ie, sleep and physical activity), we will use the same approach described for our first aim. That is, we will evaluate the overall treatment effect and how this effect changes with time. Unique in this evaluation, we will test these relationships using continuous outcome (ie, the amount of time spent on these health behaviors) as well as the likelihood of meeting the threshold for recommended levels of physical activity (≥150 minutes of moderate to vigorous physical activity/week) and sleep (>7 hours/night). That is, we are interested in finding out whether participants who receive the innovative JIT intervention were more likely to meet recommended levels of physical activity or sleep.

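### Total sleep time is defined as the whole onset-to-awakening interval, so as written it includes wake after sleep onset and exceeds actual sleep by that amount every night

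*Protocol article*

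**What the plan says.** All the sleep definitions stand in one paragraph of the protocol article, under Objective Sleep:

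- Total sleep time: "Total sleep time will be calculated by the number of minutes between sleep onset and awakening".
- WASO: "Wake after sleep onset is the total time spent being awake between sleep onset and awakening".
- Sleep efficiency: "sleep efficiency will be calculated as the proportion of actual sleep from sleep onset to awakening relative to the total sleep duration interval".
- Source of the variables: "Sleep intervals and relevant sleep outcomes will be derived using a previously validated algorithm [36" (the number is a literature citation; the algorithm's formula is not given).

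The other listed sleep outcomes are nap measures. Total sleep time is therefore the only device-based duration of night sleep.

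Under Proposed Analyses and Analytical Approach, aim 2 is analyzed in two ways. One uses a continuous outcome, described as "the amount of time spent on these health behaviors". The other uses "the likelihood of meeting the threshold for recommended levels of physical activity" and a corresponding threshold for "sleep (>7 hours/night" (closing bracket omitted). Neither statement names the sleep variable or its data source. A second source of sleep duration exists: of the daily morning questionnaire, the Morning Survey section says "This survey will assess the duration and quality of the previous night’s sleep".

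**The concern.** A count of minutes from sleep onset to awakening is the length of the sleep period. It equals time asleep only on a night with no waking. The efficiency definition shows that the authors distinguish actual sleep from the interval that contains it, yet the total sleep time sentence gives the interval. Actual sleep in minutes, the numerator of efficiency, is not itself a listed outcome.

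Two things are at stake in aim 2. The continuous duration outcome would mix time asleep with time awake in bed. If the 7-hour test uses the same variable, a night could pass with less than 7 hours asleep. An intervention meant to reduce stress and perseverative thinking might plausibly act on night waking, and the duration outcome as defined does not respond to that.

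**Working it through.** The plan states no figure that depends on this definition, so there is nothing to reproduce. The check is an identity followed by an illustration.

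**1. Identity (from the Objective Sleep definitions).** Let I be the minutes from sleep onset to awakening, W the WASO, and S the minutes asleep. Every minute of the interval is either sleep or wake, so

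I = S + W.

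Total sleep time as written is I. Hence total sleep time as written − S = W ≥ 0 on every night.

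**2. Consequence for change and for the group contrast.** Taking differences, ΔI = ΔS + ΔW.

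- Less waking in an unchanged interval: ΔW = −d and ΔS = +d, so ΔI = 0. The gain of d minutes asleep does not appear in total sleep time. It does appear in WASO and in efficiency (S/I).
- More waking with a later final awakening and no more sleep: ΔS = 0 and ΔW = +d, so ΔI = +d. This counts as more sleep.
- If mean WASO is the same in both arms, the between-arm difference in mean I equals that in mean S.

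**3. Consequence for the 7-hour threshold, if it uses this variable.** A night passes when I > 420, that is, when S > 420 − W. Nights with 420 − W < S ≤ 420 are counted as meeting the threshold although actual sleep does not exceed 7 hours. For a night with I = 421 minutes and an assumed W:

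| Assumed WASO (min) | Actual sleep (min) | Efficiency | Actual sleep needed to pass as written (min) |
|---|---|---|---|
| 20 | 421 − 20 = 401 | 95.2% | > 400 |
| 40 | 421 − 40 = 381 | 90.5% | > 380 |
| 60 | 421 − 60 = 361 | 85.7% | > 360 |

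**4. Illustrative share of nights affected.** The documents give no mean, SD or WASO, so every input here is an assumption: I is normal with mean 7.5 h and SD 1.1 h, and W is constant across nights.

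- As written: 1 − Φ((7 − 7.5)/1.1) = 67.5% of nights exceed 7 h.
- With W removed: 1 − Φ((7 − (7.5 − W/60))/1.1) = 56.0%, 44.0% and 32.5% for W = 20, 40 and 60 minutes.
- Differences: 11.5, 23.5 and 35.0 percentage points.

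With other assumed inputs (interval mean 420 to 460 minutes, SD 60 to 75 minutes), the fall is about 10 to 13 points for a WASO of 20 minutes, 20 to 26 points for 40 minutes, and 29 to 38 points for 60 minutes.

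**The case against.** The strongest reply is that the variables come from a validated algorithm and scoring by two trained staff. If that algorithm returns minutes scored as sleep, the sentence is loose wording in a condensed article and no derived value is wrong. This is possible, and the document cannot settle it. It does not rescue the sentence, which gives an explicit formula that an analyst could follow to the wrong variable. It does mean that a reader should not infer that the trial's sleep data are themselves wrong.

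A reader might also infer that the 7-hour endpoint is overstated as a matter of fact. The analysis section names no variable for that test, and self-reported duration is also collected each morning. Use of the device measure is the natural reading, but it is still an inference.

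A third tempting inference is bias in favor of the intervention. The documents do not support it: the definition is identical in both arms and does not by itself inflate the contrast. Reduced night waking is not lost to the trial either, since WASO and efficiency are listed outcomes and actual sleep can be recovered as the interval minus WASO.

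Finally, the percentages rest wholly on assumed inputs, and an assumed mean close to the cut-off makes the shifts large. That is correct, and they should be read only as illustration.

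**Conclusion.** The point stands as a wrong definition of a secondary-aim outcome, of moderate severity. From the article's own definitions, total sleep time as written exceeds actual sleep by WASO on every night; this part needs no assumption. The effect on the 7-hour test is conditional on that test using this variable. Its direction is then certain (the share of nights meeting the threshold can only be overstated), but its size is unknown. About 12 to 35 points is an illustration for an assumed WASO of 20 to 60 minutes, interval mean 7.5 h and SD 1.1 h.

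The practical harm is a duration outcome that does not respond to reduced waking within an unchanged interval and that credits longer waking with a later awakening as sleep. The stress-response outcomes of the primary aim, the randomization and the sample size do not depend on this definition.

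**What to change.** Before analysis:

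1. Define total sleep time as minutes scored as sleep, that is, the onset-to-awakening interval minus WASO.
2. Confirm that the output of the cited algorithm matches this definition. If it already does, only the sentence needs correction.
3. Keep the interval under its own name, such as sleep period duration, and use it as the denominator of efficiency.
4. State under the proposed analyses that the threshold of more than 7 hours a night is applied to the corrected total sleep time.

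The cost is about one line of text and one line of derivation code. WASO is already a planned outcome, so no new data are needed. The Results section reports that analyses have not begun, and the Randomization section keeps group assignments masked until all data are entered. The change can therefore be made and dated before unmasking.

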#### Objective Physical Activity

The physical activity data will be aggregated into 1-minute epochs. Using the sleep and wake times from the sleep data, all sleep periods will be excluded in the subsequent data aggregation process. Furthermore, any continuous sitting or standing events that are >5 consecutive hours will be classified as nonwear and will also be excluded. The remaining valid wake period will be classified into either time spent sedentary, standing, or stepping. Time spent stepping will further be classified into time spent in light physical activity or moderate to vigorous physical activity using the 100 steps per minute cut point [37]. Other relevant objective physical activity outcome variables will include step count and number of sit-to-stand transitions. The physical activity data will be further aggregated depending on the level of analysis as necessary (eg, hourly, daily, and person-level summary).

### JIT Intervention

#### General Approach

In line with the principles of the JIT intervention approach, our goal was to develop empirically supported stress management content that is delivered during particularly stressful moments. It uses a nudge framework [38] to help a person reorient to a nonstress state via improved affect and reduced perseverative and maladaptive cognitions. More broadly, each nudge aims to help build a diverse toolkit of stress management skills that can be implemented in everyday life. Furthermore, this allows us to implement a personalized approach to intervention delivery using real-time information specific to the individual at a given moment to deliver content at moments of presumptive risk or need [39].

#### Intervention Content

The development and testing of our intervention content have been described previously [40]. Briefly, we developed our intervention content within 4 broad categories: relaxation, response modulation, positive experiences, and resource buffers.

#### Relaxation

These techniques aim to shift the body from a state of elevated or negative arousal to a relaxed or neutral state. Participants could do controlled breathing, deep breathing, progressive muscle relaxation, or an object-focused meditation.

#### Response Modulation

These techniques aim to promote self-regulatory behavior, in particular, to manage emotions, promote efforts to change thoughts and associated emotions to a more positive meaning, reduce impulsive behavior, and focus attention away from emotion-eliciting situations or thoughts. Participants could perform a reappraisal task to learn how to rethink negative situations, an attentional deployment task to train them to focus on positive stimuli, a third-party observer task that asks them to imagine how an outsider would view their stress, or an affect labeling task to encourage the ability to use words to self-describe negative emotional events.

#### Positive Experiences

This category aims to facilitate engagement in activities that can induce positive mental states. Participants could imagine saying positive statements to themselves, reacting to positive imagery, engaging in a gratitude exercise, or a reminiscing task that engages them to relive a positive event in their lives.

#### Resource Buffers

This category aims to increase the quality of life at the moment to enhance function and resilience. Participants could engage in a self-affirmation task to embrace those facets of their life that are most positive, a self-efficacy task to encourage them to find moments they have successfully dealt with life events, a social comparison task that allows them to learn from others who have successfully dealt with stress in their lives, or a best possible self activity (imagining an idealized version of themselves and how they might achieve that self).

#### Intervention Types

##### Overview

The intervention content was developed to be appropriate for everyday life, including the consideration of general availability to engage with the intervention content. Therefore, we developed 2 intervention types of differing lengths and time of day availability, and all content was intended to be displayed to the participant on a smartphone. Each activity is intended for the participant to do independently, not requiring interaction with others.

##### Microinterventions

These very brief interventions (ie, microinterventions) are no more than 1 to 2 minutes in duration. This suite of microintervention content includes 16 brief videos, including 4 microinterventions across each of the 4 categories described above. For any given participant randomized into the JIT condition, when an intervention moment is identified (refer to Intervention Delivery section), 1 of the 16 microinterventions will be randomly selected from the suite of videos and presented to them on the smartphone. To maximize engagement and increase the potential for exposure to the different skills and activities, each time an intervention is delivered, it will not be placed back in the pool of available videos for potential delivery until all 16 videos have been used.

Once a microintervention is initiated, participants will receive an audible alert from the phone, and once activated, they will be notified that their stress levels appear elevated and that a recommended intervention is available to help reduce their stress. Next, they will receive a description of the activity they will engage in and how to be prepared to do it most effectively. They will then initiate the intervention video on the smartphone and follow the guided instructions. Each activity is designed so that previous training is unnecessary, but continued engagement may increase one’s enjoyment and ease in doing the activity. At the end of each intervention, we will ask the participant to consider what worked with the intervention and plan how to use it in a future moment of stress. To this end, participants must consider when they are stressed and thus engage in some self-monitoring of their behaviors. Furthermore, by encouraging participants to use the activity on their own, they may be more likely to practice and improve their skills.

##### End-of-Day Intervention

We also wanted to provide a longer, more comprehensive intervention that covered the various domains of our broader intervention approach while providing an opportunity for more focused skill-building. This 20-minute singular intervention will be delivered in the evening when people may have more time to engage in the focused activity. It comprises multimodal components that cover several broad domains and represents a progression of many of the techniques and categories noted above. The goal is to guide an individual through more extensive training to reduce stress via improved affect and reduced perseverative cognitions. It is intended to be repeated to build general skills in the broad domains it covers. Similar to what was outlined previously, participants will receive stressor-focused framing before and after the intervention.

